### Randomization

Patients participating in the study are randomized after a run-in period, using block randomization at the patient level, at an 1:1 allocation ratio into either one of the two groups: control group or experimental group. Prior to the start of the study the randomization list was generated by a statistician (RT) using a macro [37] in SAS Enterprise Guide 7.13 (SAS Institute Inc., Vary, NC, USA) that automates the random assignment to treatment groups. To prevent predictability of the blocked randomization, block sizes were random and hidden to the researchers and therapists. Since age of the patient can be a confounding variable, in particular being above or below the age of 18 years, age was a stratification factor. Envelopes were numbered in the same order as the randomization list and the group allocation was put in the envelopes after which they were sealed, so that these could be taken to the home of the participant and revealed accordingly.

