### Statistical analysis

#### Power calculation

To our knowledge there was no (multi) systemic intervention study carried out among kidney transplant recipients at the time this project commenced, making it difficult to conduct a power analysis based on a comparable study. Therefore, the power calculation is based upon a behavioral intervention study among a group of heart, liver and lung transplanted patients [72]. The intervention group showed an adherence proportion of 95.1% and the control group a proportion of 79.1%. As the MARS-intervention is more intensive than the intervention of Dobbels et al. [72] we will perform an interim analysis when half of the participants have been included. We applied a 2-sided alpha of 0.029 and a power of 0.80. Anticipating a drop-out of 10%, this led to a target of 81 participants in both groups, a total of 162.

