#### Primary study parameter

The primary outcome, the proportion of participants that is adherent more than 95% of the 180 days (T1-T2) in both randomization groups as measured by EM, will be analyzed with a chi-test with continuity correction. The cut-off score of 95% is in accordance with the criteria of the Basel Assessment of Adherence to Immunosuppressive Medications Scale: BAASIS interview [48].

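### The target of 81 per group gives about 69% power, not 80%, for the continuity-corrected chi-square test that the protocol names as its primary analysis

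*Protocol article*

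**What the plan says.** The Power calculation section of the protocol article takes its planning rates from a behavioural intervention trial in heart, liver and lung recipients: "The intervention group showed an adherence proportion of 95.1% and the control group a proportion of 79.1" per cent. It continues: "We applied a 2-sided alpha of 0.029 and a power of 0.80". The target follows: "Anticipating a drop-out of 10%, this led to a target of 81 participants in both groups, a total of 162". The section does not name the test or formula behind that number. It also announces that "we will perform an interim analysis when half of the participants have been included".

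The Primary study parameter section fixes the analysis: the proportion of participants above the 95% adherence threshold between T1 and T2 "will be analyzed with a chi-test with continuity correction". The Randomization section gives equal allocation ("at an 1:1 allocation ratio into either one of the two groups").

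**The concern.** The continuity correction makes the chi-square test more demanding, and at fewer than 100 patients per group the difference is material. A sample size derived for the uncorrected test is too small for the corrected one. The target of 81 can be reproduced from an uncorrected calculation, and no corrected calculation tried at two-sided 0.029 gives it.

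This is the only primary test. If the mismatch is real, the power in the protocol is wrong for the analysis it declares, and an effect of the planned size is missed more often than readers are told. The Procedure section adds that inclusion was stopped because of Covid-19, so recruiting more patients may not be possible.

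**Working it through.** **Inputs** (Power calculation, Randomization and Primary study parameter sections): p1 = 0.951, p2 = 0.791, difference 0.160, two-sided alpha 0.029 (z = 2.1835), power 0.80 (z = 0.8416), 1:1 allocation, 81 randomised per group, 10% drop-out. The number analysed is 81 × 0.9 = 72.9, about 73 per group.

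**Step 1: reproduce the target.** The arcsine formula without correction is n = 2[(z_α + z_β)/h]², with h = 2·arcsin√0.951 − 2·arcsin√0.791 = 2.6952 − 2.1920 = 0.5032. This gives n = 2 × (3.0251/0.5032)² = 72.3. Then 72.3/0.9 = 80.3, rounded up to 81. (Rounding to 73 first and adding 10% also gives 80.3, so 81; 73/0.9 would give 82.)

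**Step 2: other formulas at two-sided 0.029.**

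| Method | Analysed per group | Randomised per group (÷ 0.9) |
|---|---|---|
| Arcsine, uncorrected | 72.3 | 81 |
| Unpooled normal, uncorrected | 76 | 85 |
| Pooled normal, uncorrected | 80 | 89 |
| Exact enumeration, corrected | 87 | 97 |
| Unpooled normal, corrected | 88 | 98 |
| Pooled normal, corrected (Fleiss) | 92 | 103 |

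The Fleiss figure starts from the pooled n = 79.04 and applies n_c = (n/4)[1 + √(1 + 4/(n × 0.16))]² = (79.04/4)(1 + 1.1473)² = 91.1, so 92.

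**Step 3: power of each test at the planned size.** For every pair of counts (a, b), the 2×2 chi-square statistic was computed with and without the correction. The binomial probabilities of all pairs exceeding the 0.029 critical value were then summed.

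| Analysed per group | Uncorrected | Corrected |
|---|---|---|
| 73 (after 10% loss) | 0.799 | 0.693 |
| 81 (no loss) | 0.846 | 0.758 |
| 86 | 0.869 | 0.794 |
| 87 | 0.874 | 0.800 |

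A normal approximation for the corrected test agrees. At 73 per group, subtracting 1/73 from the difference gives (0.1463 − 2.1835 × √(0.2247/73)) / √(0.2119/73) = 0.467, hence power 0.680.

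**Step 4: credit the interim look.** The protocol does not say what level applies at each look. Assume 0.029 at both, with 36 per group at the interim and 73 at the end. The probability of rejecting at either look is then 0.705 corrected and 0.817 uncorrected.

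**Step 5: what the correction does to the type I error.** With 73 per group, nominal level 0.029 and common rates from 20% to 90%, the true size is 0.011 to 0.020 with the correction and 0.025 to 0.030 without. At the average planning rate, (0.951 + 0.791)/2 = 0.871, the sizes are 0.013 and 0.029. The smallest expected cell count there is 0.129 × 73 = 9.4.

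**The case against.** The strongest objections concern the remedy and the weight of the point; the arithmetic is not in dispute.

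- **Interim counts are small.** At 36 per group the smallest expected count is 0.129 × 36 = 4.6, under the usual threshold of 5, so the final-look count cannot vouch for both looks. That is correct. By enumeration, however, the uncorrected test's size at 36 per group peaks at 0.031, so the practical harm is slight.
- **The uncorrected test slightly exceeds its nominal level.** It peaks at 0.0302 against 0.029 at the final look. With 0.029 assumed at both looks, the overall error peaks at about 0.052, against about 0.030 with the correction. This stands as a caveat.
- **A correction is a legitimate conservative choice.** Agreed. The error is the mismatch between sizing and test, and restating the power resolves it too.
- **The sizing method is inferred.** The protocol names none, so the arcsine route is only consistent with its figure. The shortfall does not depend on that inference, because it is computed from the stated sample size, alpha, rates and drop-out.
- **The planning rates are borrowed and uncertain.** With the control rate at 79.1%, an intervention rate of 97% would give the corrected test 0.855. This shows sensitivity to the assumption, but the stated 0.80 is a claim about the protocol's own rates and fails there.
- **Timing.** Patients and therapists are unblinded, and the article does not say whether the interim analysis has been done. Changing to a less conservative test after seeing comparative data would be open to criticism. This limits when the preferred fix may be used.

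**Conclusion.** The concern holds. At the protocol's own rates, alpha, sample size and drop-out, the declared primary test has power 0.693, about 11 percentage points below the stated 0.80. The risk of missing the planned effect is about 31% at the final analysis, or 29.5% if rejection at the interim is also counted and 0.029 is used at each look. Reading 81 as the number analysed raises corrected power only to 0.758. The defect costs power and does not raise the false-positive rate. If recruitment ended short of 162, power is lower still.

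**What to change.** Reconcile the Power calculation and Primary study parameter sections in one of two ways.

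1. **Preferred, if no between-arm comparison of electronic monitoring data has been seen, including at the interim:** replace the corrected test with the uncorrected Pearson chi-square in the Primary study parameter section. This restores power to about 0.80 at the existing target. Record the date of the change, and state that the level is held essentially, not strictly, at nominal. State also which alpha applies at each look, since the overall error depends on it.
2. **If comparative data have been seen, or the correction is kept by choice:** leave the test as it is and restate the power as about 0.69 with 73 analysed per group. Keeping both the correction and 80% power would require 97 randomised per group by exact calculation (194 in total), or 103 by the Fleiss formula (206 in total).

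Either of the first two courses costs a sentence in the protocol or SAP and no additional patients. Re-sizing would add 32 to 44 participants to the planned 162, which looks impractical now that inclusion has stopped.

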#### Primary study parameter

The primary outcome, the proportion of participants that is adherent more than 95% of the 180 days (T1-T2) in both randomization groups as measured by EM, will be analyzed with a chi-test with continuity correction. The cut-off score of 95% is in accordance with the criteria of the Basel Assessment of Adherence to Immunosuppressive Medications Scale: BAASIS interview [48].

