**Primary objective**					
To test the effectiveness of the MARS- intervention (experimental group) in promoting medication adherence as measured by Electronic Monitoring in comparison to CAU (control group).	Data from Electronic Monitoring		X	X	X

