### Procedure

Inclusion commenced in September 2018, but inclusion is recently stopped due to Covid-19. Data collection is still ongoing. Participants are being recruited from one academic hospital in the Netherlands where they received their kidney transplant or from the local hospital after referral for post-transplant care. Patients who are eligible for the study are informed about the study by the healthcare professional at the end of their regular appointment. Thereafter the healthcare professional or someone from the research team hands out written information on the study (PIF). The healthcare professional was provided with a standardized script on introducing the study. After having time to consider participation, the researcher contacts the patients by telephone to provide additional information (when needed), answer questions, ask for consent and make an appointment to obtain written consent. This appointment can take place at the patient’s home and the important other is also invited to attend. After written consent from both parties is obtained, the first questionnaires are completed (T0) and the electronic monitoring device is explained and handed out. Since evidence suggests that adherence will be statistically higher when patients start to use the electronic monitoring device [38], a run-in period of 35 days (+/− 7 days) is incorporated. A second appointment is made to coincide with the end of the run-in period (T1), during which a second set of questionnaires is completed by patient and important other, and EM data is collected. Group assignment is revealed after questionnaires have been completed. For the following 6 months patients allocated to the experimental group receive the intervention and the control group receives CAU. Six months after T1 participants are asked to complete questionnaires and EM data is collected (T2). Subsequently, patients continue using the EM device for the follow-up period of 6 months and questionnaires are also completed at the end of this 6 months (T3) (see Fig. 1 for flow-diagram) .

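### The primary test is valid but uses neither the age stratum nor the run-in electronic-monitoring adherence, both already in hand, and so gives up a modest, assumption-dependent amount of power

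*Protocol article*

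**What the plan says.** Under Statistical analysis, Primary study parameter, the endpoint is binary for each patient: adherent or not at the 95% threshold over the 180 days from T1 to T2. The section says that this proportion "in both randomization groups as measured by EM, will be analyzed with a chi-test with continuity correction". It names no stratum and no covariate.

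Two pieces of pre-allocation information are described elsewhere in the article:

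- **Age.** The Randomization section treats age as a possible confounder, "in particular being above or below the age of 18 years, age was a stratification factor".
- **Run-in EM.** The Procedure section says that "a run-in period of 35 days (+/− 7 days) is incorporated", with the device handed out at T0 and read at T1. The Randomization section adds: "Patients participating in the study are randomized after a run-in period". Table 1 lists "Data from Electronic Monitoring" at T1, T2 and T3.

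Under Secondary study parameters, the multilevel models for continuous and binary secondary outcomes include age and the T1 measure. The sustainability model includes T1 adherence.

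**The concern.** Run-in EM adherence is the outcome variable itself, measured with the same device before allocation is known. Entry depends on self-report or on a report by a professional or someone in the social network (Study population), and the article excludes nobody for high run-in EM adherence. Patients can therefore start from quite different levels. With about 73 evaluable per arm, a chance imbalance in that starting level passes uncorrected into the primary comparison.

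The age stratum was built into the randomisation because age was thought to matter, but the primary analysis does not reflect it. At stake are some power and some precision in the main result, from data that the trial already plans to collect.

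**Working it through.** **Inputs.** From Power calculation: rates 0.951 and 0.791, two-sided alpha 0.029, power 0.80, drop-out 10%, 81 per group. From Randomization: 1:1 allocation, strata below and above 18. Not in the documents, hence assumed: how strongly run-in EM predicts the outcome, the share of patients under 18, and how much age matters.

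**1. Reproduce the stated sample size.** Arcsine formula, no continuity correction: n = 2(z₁ + z₂)² / h², with z₁ = 2.183, z₂ = 0.842 and h = 2·arcsin√0.951 − 2·arcsin√0.791 = 2.695 − 2.192 = 0.503.

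This gives n = 72.3 per arm, and 72.3 / 0.9 = 80.3, so 81. The stated figure is reproduced. Evaluable patients: 81 × 0.9 = 72.9, so 73 per arm.

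**2. Exact power of the crude tests.** Summing binomial probabilities over all 2x2 tables with 73 per arm, critical value 4.77 (chi-square, 1 df, alpha 0.029):

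- planned test with continuity correction: 0.693
- same test without correction: 0.799
- size at a common rate of 0.871: 0.013 corrected, 0.029 uncorrected

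The correction alone costs 0.799 − 0.693 = 0.106. The uncorrected test is therefore the fair reference for what adjustment adds.

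**3. Adjustment for run-in EM.** Simulation with 4,000 trials per setting: logit P(adherent) = a + b·x, where x is standardised run-in adherence and a is set in each arm so that the marginal rates stay 0.951 and 0.791. Treatment is tested in a logistic model with x as covariate.

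| b per SD | correlation (control arm) | uncorrected crude | adjusted, score / LR | gain in points, score / LR |
|---|---|---|---|---|
| 0 | 0 | 0.792 | 0.787 / 0.797 | −0.5 / 0.6 |
| 0.5 | 0.20 | 0.798 | 0.811 / 0.823 | 1.3 / 2.5 |
| 1.0 | 0.35 | 0.799 | 0.841 / 0.852 | 4.2 / 5.3 |
| 1.5 | 0.46 | 0.807 | 0.874 / 0.884 | 6.7 / 7.7 |
| 2.0 | 0.53 | 0.812 | 0.918 / 0.924 | 10.6 / 11.2 |

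Adjustment thus adds about 0 to 11 points. Simulated size was 0.025 to 0.031 for the score test and 0.028 to 0.034 for the likelihood-ratio test. The Monte Carlo standard error is √(0.029 × 0.971 / 4000) = 0.003, so both agree with 0.029.

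**4. Age stratum alone.** A Cochran-Mantel-Haenszel test without correction (6,000 trials per setting; 5% to 20% under 18; log-odds shift 0 to 2) had power 0.80 to 0.85. The uncorrected crude test had 0.80 to 0.82. Setting by setting, the gain is about 0 to 3 points.

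**5. How many events the model has.** Expected non-adherent patients at the planning rates: 0.049 × 73 + 0.209 × 73 = 3.6 + 15.3 = 18.8, about 19.

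**Limit of the check.** Steps 3 and 4 took one covariate at a time and used no penalty. The combined penalised model was not simulated.

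**The case against.** The strongest reply is that the planned test is sound. It follows from randomisation, needs no model, compares proportions directly and does not inflate type I error. All of this stands, so the point concerns efficiency and does not identify an error.

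A second reply is that run-in EM may predict poorly. The Procedure section introduces the run-in because adherence is higher when patients first use the device, so early readings may be inflated. This also stands: no document shows that run-in EM is the strongest predictor, and at zero correlation adjustment gains nothing over the uncorrected test.

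A third reply is that about 19 events are few for a model with treatment and two covariates. That is a real cost and shapes the fix.

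Three stronger readings might be inferred, and the documents do not support them:

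- **That adjustment recovers the whole gap between the planned test and an adjusted model.** About 10 points of that gap come from dropping the continuity correction.
- **That ignoring the stratum makes the planned test markedly conservative.** The low size (0.013 against 0.029) appears without any age effect and goes away when the correction is removed.
- **That the article consistently adjusts everything but the primary test.** The comparison on the composite adherence score is also a crude chi-test, and the sustainability and monthly models list no age term. The sustainability model already uses T1 adherence, though only as a secondary analysis.

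**Conclusion.** The point holds as an efficiency improvement. At the planning rates, with 73 evaluable per arm and alpha 0.029, adjusting for run-in EM would raise power by about 0 to 11 points over the uncorrected test's 0.80. The size depends on an assumed correlation of 0 to about 0.5. The age stratum adds about 0 to 3 points; the better argument for including it is that the analysis should match the stratified randomisation.

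That neither item enters the primary test is certain from the text. The benefit is not: it rests on the assumed correlation and on the planning rates being right. The planned test's power of 0.69 is due to the continuity correction and is a separate point.

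**What to change.** Before any unblinded data are analysed, make the primary analysis a prespecified logistic regression of the 95% endpoint on three terms: treatment, age stratum (below 18, or 18 and above) and continuous run-in (T0 to T1) EM adherence. Fix Firth's penalty in advance. With about 19 non-adherent patients expected, separation is possible, and choosing the penalty only after seeing it would make the method depend on the data. Add no further covariates. Report the standardised risk difference with its confidence interval, so that the result stays on the scale of a difference in proportions, and keep the crude 2x2 comparison as supportive.

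No new data are needed. The costs are the analysis wording, one model and a primary test that relies on a model with few events. The Power calculation section also plans an interim analysis at half inclusion, and the article does not say whether it has taken place. The change should record its timing relative to that look.

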#### Secondary study parameters

The proportions of adherent participants based on the CAS in both randomization groups will be analyzed with a chi-test with continuity correction. The influence of biological markers on adherence will be analyzed with a logistic regression.

The continuous secondary outcomes will be analyzed with linear multi-level regression analyses. The patients form the upper level, their measures at T1 and T2 the lower level. The covariance structure will be determined with the deviance score applying restricted maximum likelihood. Treatment group, T2, the group-T2 interaction and age will be postulated as fixed effects. In case of an abnormal distribution of the scores, an appropriate transformation (logarithmic, polynomial or Blom [73]) will be applied. If no satisfying transformation can be found, the outcome will be dichotomized on the median, and a multilevel logistic regression analysis will be performed. Binary outcomes will be analyzed with multilevel logistic regression analysis, using the same levels and fixed effects as described for linear multi-level regression analysis.

To analyze whether the intervention is sustainable 6 months after the treatment, a logistic multilevel analysis will be applied including the T1, T2 and T3 measures. Adherence will be the dependent variable, and treatment group, T2, T3 and group-time interactions will be the fixed effects. The group-T2 interaction effect will present the differential intervention effect, and the T2-T3-group contrast is the effect of interest for sustainability.

To answer the question when the intervention influences the adherence most, a multi-level logistic regression analysis will be applied. The EM devices can be read every 30 days, resulting in a baseline and 6 repeated measures (at 65, 95, 125, 155, 185 and 215 days). The fixed part of the model will include treatment group, the six follow-up time points and interactions.

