### Study population

#### Patients

The study population consists of kidney transplant recipients, aged 12 years and older, with no limitation to time since transplantation. Patients are required to have a subscription of IM and have a functioning graft at the time of inclusion. Graft functioning may be deteriorating, but as long as IM is required and the patient is not expected to be on dialysis within the next 3 months they can be included. In order to avoid convenience sampling multiple ways of assessing eligibility are being used. Kidney transplant recipients are eligible for inclusion when non-adherence is signaled by either themselves (self-report), or by the nephrologist or nurse practitioner (collateral report – professional) or someone in the patient’s social network (collateral report- social network). These three indicators combined form a composite adherence score (CAS). An affirmative answer on one (or more) of these indicators is sufficient to invite the recipient to participate. A CAS is more sensitive than using a single measure of non-adherence [31, 34–36]. Furthermore, non-adherent patients who do not explicitly acknowledge their non-adherence as a problem can be identified using the CAS. Professionals form an impression of adherence through, for example, conversations with the patient, clinic attendance and blood assay monitoring. Potential participants who meet any of the following criteria will be excluded from participation: 1) patients classified as adherent on all three of the indicators forming the CAS, 2) patients on dialysis or who are expected to start dialysis within the next 3 months, 3) patients who do not understand the Dutch language, 4) patients prior to their first transplant, and 5) patients with severe psychopathology or ongoing psychological treatment. In contrast with most other studies, patients with cognitive limitations (incapacitated) are not excluded from participation because their representative(s) and social network can be involved in the intervention and give complementary information regarding problems the patient is facing.

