#### Secondary outcome measures patient

##### Medication adherence

In addition to EM, other secondary outcome measures are also used to assess medication adherence. This is in line with the suggestion of Schafer-Keller et al. [31] to combine several measurements to reach maximum validity. We calculate the Composite Adherence Score (CAS) combining the following measures:
Patient self-report about non-adherence (Basel Assessment of Adherence to Immunosuppressive Medications Scale; BAASIS©-interview).Collateral report – important other about patients’ non-adherence using an Adjusted Basel Assessment of Adherence to Immunosuppressive Medications Scale; BAASIS©-interview.Collateral report – professional about patients’ non-adherence based on varying medication blood levels or behavioral indicators such as missed appointments.

The BAASIS takes both taking and timing into account, as well as drug holidays, reduction of medication doses, and persistence over the last 4 weeks. An affirmative answer on missing a dose (taking), taking IM ≥ 2 h before or after prescribed dosing time (timing), reducing the IM dose, or stopping taking medication completely (persistence) leads to being categorized as non-adherent. Patients also rate their own adherence using a visual analogue scale ranging from 0% (never take medication as prescribed) to 100% (always take medication as prescribed). The BAASIS is recommended for the use as a self-report measure among transplant recipients [1, 48]. An adjusted version of the BAASIS is used for the collateral report of the important other regarding the medication adherence of the patient. The important other is presented with the same questions as the patients on the IM adherence of the patient. Additional to the yes/no, the important other is allowed to answer I don’t know.

The collateral report from the professional is based on a yes/no answer as to whether they think a patient is adherent.

Furthermore, medical data derived from the medical records is also used to give an impression of adherence. We calculate intra patient variability (IPV) using whole blood concentrations of tacrolimus in multiple measurements over time within patients. The method previously described by Borra et al. [49] is used to make this calculation. The following transplant outcomes are collected: rejection of the graft (yes/no), graft loss (yes/no) and kidney functioning (eGFR).

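### The composite adherence score gets a conservative chi-test that ignores its T1 value and the age stratum, and the text does not exempt it from the general rule for binary outcomes

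*Protocol article*

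**What the plan says.** All references are to the Protocol article.

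- **What the CAS is.** Under Secondary outcome measures patient, Medication adherence: "We calculate the Composite Adherence Score (CAS) combining the following measures". The three measures are patient self-report, the important other's report and the professional's report. Each is classed as adherent or non-adherent, so the CAS is a binary secondary outcome. Table 1 lists all three at T0, T1, T2 and T3.
- **The test named for it.** Secondary study parameters opens with: "The proportions of adherent participants based on the CAS in both randomization groups will be analyzed with a chi-test with continuity correction". No T1 value and no age term enter this test.
- **The general rule.** The next paragraph, which begins with the continuous secondary outcomes, ends: "Binary outcomes will be analyzed with multilevel logistic regression analysis, using the same levels and fixed effects". The levels are: "The patients form the upper level, their measures at T1 and T2 the lower level". The fixed effects are: "Treatment group, T2, the group-T2 interaction and age will be postulated as fixed effects".
- **Design facts.** Patients are randomised after the run-in, "at an 1:1 allocation ratio", and "age was a stratification factor", split at 18 years. Procedure has the T1 questionnaires completed before the allocation is revealed. Under Study population, those excluded include "patients classified as adherent on all three of the indicators forming the CAS".

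**The concern.** There are two separate issues.

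First, both sentences cover the CAS as written. The general sentence is not limited to the remaining binary outcomes, and no order of precedence is given. The two rules estimate different things: a crude difference in proportions, or a difference in change from T1. They can give different p-values on the same data.

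Second, the test named for the CAS leaves information unused. T1 is measured before allocation is known, so it is a legitimate covariate. Age was important enough to stratify on and is a fixed effect for the other secondary outcomes. The continuity correction also holds the test below its nominal level. At stake is the sensitivity of one of the secondary adherence measures set beside electronic monitoring. The validity of the trial is not at stake.

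**Working it through.** **Step 1. Number of evaluable patients.** The article states no sample size for the CAS. The figure for the primary outcome is 81 per arm, with 10% drop-out, two-sided alpha 0.029, power 0.80, and rates of 95.1% and 79.1%. It reproduces with the arcsine formula n = 2[(z_a + z_b)/h]², where h = 2(asin√0.951 − asin√0.791) = 0.503, z_a = 2.183 and z_b = 0.842. This gives n = 72.3, and 72.3/0.9 = 80.3, rounded up to 81. Evaluable patients per arm are 81 × 0.9 = 72.9, taken as 73.

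**Step 2. Assumptions for the CAS.** The documents give no CAS rates, no T1–T2 correlation and no share of patients under 18. Assumed here: 50% against 30% CAS-adherent at T2, two-sided 0.05, T1 adherence of 10% or 30%, and tetrachoric T1–T2 correlation of 0.4, 0.6 or 0.75.

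**Step 3. Cost of the continuity correction.** With equal arms the corrected test rejects when |p1 − p2| exceeds 1.96·√(2p̄(1 − p̄)/n) + 1/n.

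- Null standard error: √(2 × 0.4 × 0.6/73) = 0.0811. The threshold is 0.1589 uncorrected and 0.1589 + 0.0137 = 0.1726 corrected.
- Standard error under the alternative: √((0.25 + 0.21)/73) = 0.0794.
- Power uncorrected: Φ((0.2 − 0.1589)/0.0794) = Φ(0.517) ≈ 0.70. Power corrected: Φ((0.2 − 0.1726)/0.0794) = Φ(0.345) ≈ 0.63.
- Exact binomial enumeration gives 0.706 and 0.644, a loss of 6 points.
- Size with both arms at 30%: null standard error √(2 × 0.3 × 0.7/73) = 0.0758, so the effective critical value is 1.96 + 0.0137/0.0758 = 2.14, a size of about 0.032. The exact value is 0.0316 corrected and 0.0504 uncorrected.

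Exact power for other assumed rates at 73 per arm:

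| T2 rates | Uncorrected | Corrected |
|---|---|---|
| 50% vs 30% | 0.71 | 0.64 |
| 45% vs 25% | 0.72 | 0.66 |
| 40% vs 20% | 0.76 | 0.70 |
| 30% vs 15% | 0.59 | 0.51 |

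**Step 4. Value of T1.** Simulated power of a logistic regression of T2 CAS on group and T1 CAS, 73 per arm, 50% vs 30%:

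| T1 adherent | corr. 0.4 | corr. 0.6 | corr. 0.75 |
|---|---|---|---|
| 30% | 0.72 | 0.76 | 0.82 |
| 10% | 0.70 | 0.74 | 0.75 |

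The fair comparator is the uncorrected test (0.71), because it also runs at about 0.05. On that basis T1 adds between roughly 0 and 11 points (0.82 − 0.71). The rest of the gap to 0.64 is the correction.

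**Step 5. The general rule as written.** Simulated power of the group-by-T2 interaction at 72 per arm, same T2 rates, T1 adherence 10–30%:

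| Latent correlation | Interaction | Corrected chi-test |
|---|---|---|
| 0.3 | 0.29–0.46 | 0.62–0.64 |
| 0.5 | 0.32–0.53 | 0.63 |
| 0.7 | 0.34–0.64 | 0.62–0.63 |
| 0.85 | 0.36–0.77 | 0.63 |

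The interaction is clearly stronger only at correlation 0.85 with T1 adherence of 30%. A random-intercept logistic check over five settings gave 0.37–0.77.

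**The case against.** The best defence is that a sentence written for the CAS overrides a later general one. It also matches the primary analysis, which uses the same corrected test, so it looks deliberate. That largely stands. A reader might infer that the plan leaves the CAS result open to choice between two rules, but the text supports only a wording gap.

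A second defence is that the chi-test is valid and conservative, so it does not produce extra false positives. This stands in full.

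Third, a reader might credit the whole distance from 0.64 to 0.82 to ignoring T1. That is wrong. Part is the correction, and the top of the range needs both a high correlation and 30% CAS-adherent at T1. Every entrant is CAS non-adherent at inclusion, T1 is only about 35 days later, and one positive indicator is enough for non-adherence. A low T1 rate is therefore plausible, and with it the T1 gain is small.

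Fourth, the power gain is measured against a model that the article does not name. Against the article's own alternative, the interaction, the chi-test usually does better. This also stands, and it is why the remedy is not simply to apply the general rule.

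Finally, the separate contribution of age has not been quantified. Nor does the article call the CAS the main check on electronic monitoring. It is one of several secondary measures, alongside tacrolimus variability and transplant outcomes.

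**Conclusion.** The point holds in limited form. The text should state which rule governs the CAS; the specific sentence probably does. The named test is valid but runs at about 0.03 when 0.05 is intended, and it leaves a pre-randomisation measurement and the stratification factor unused.

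Under the assumed rates, correlations and T1 adherence above, power is about 0.64 as planned, 0.71 without the correction and about 0.70–0.82 with T1 adjustment. None of the CAS inputs comes from the documents. The outcome is secondary and the primary conclusion is unaffected, so this is a minor improvement.

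**What to change.** Replace the CAS chi-test sentence with a logistic regression of CAS at T2 on treatment group, CAS at T1 and age stratum (under 18, or 18 and over), reporting the adjusted risk difference with its confidence interval. Enter T1 as a covariate; do not read the effect from a group-by-T2 interaction. Reword the general sentence so that it applies to the other binary outcomes.

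The cost is a change of wording before analysis. No new data are needed, because Table 1 already schedules every CAS component at T1 and T2.
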